## Abstract

**Background:**

Cocaine use disorder (CUD) is a chronic condition that presents high relapse rates and treatment dropouts. Web-based interventions have proven to be effective when optimizing face-to-face treatments in different mental health conditions and have the potential to optimize current CUD treatments. However, web-based interventions in addictive behaviors are still limited. The aim of this study is to evaluate whether adding a web-based cognitive behavioral therapy (i.e., CBT4CBT) to standard CUD treatment, improves treatment outcomes in a Spanish sample of patients with severe CUD (which requires inpatient treatment). Additionally, we aim to explore predictive factors of treatment response and treatment gender-related differences.

**Methods:**

All individuals coming for inpatient cocaine detoxification who meet the inclusion criteria will have the possibility to be part of the study. The participants of this open-label randomized controlled clinical trial (RCT) will be allocated to treatment as usual (TAU) or TAU+CBT4CBT after the hospitalization for cocaine detoxification. During the inpatient treatment they will all receive an individualized psychological intervention. There will be six time point assessments: at 48–72 h of starting inpatient treatment, at the end of inpatient treatment and before starting day care and outpatient treatment, at the end of the 8 weeks CTB4CBT / TAU arm treatment and at three follow-up time points (1-, 3-, and 6-months post-treatment).

**Discussion:**

To the best of our knowledge, this is the first RCT that explores the efficacy of adding a web-based cognitive behavioral therapy to usual CUD treatment with patients of a clinical sample in Europe.

**Trial registration:**

IIBSP-CTB-2020-116, NCT05207228. Submitted 8^th^ of April 2021, posted 26 ^st^ of January 2022. https://clinicaltrials.gov/ct2/show/NCT05207228?cond=Cocaine+Use+Disorder&draw=2&rank=1.

## Introduction

Cocaine use disorder (CUD) is a complex condition with great impact and burden for patients, their relatives and society (1, 2). Due to its increasing incidence rate in Europe and US during the last decade (2, 3) and to its highly prevalent chronic course (4), where dropout rates are high and remission is often followed by relapse, there is a large and increasing need to improve current CUD treatments. Thus, far, no pharmacological approaches are yet approved for treating CUD, which often is a resistant-to-treat condition and is associated to significative morbidity and mortality rates (5, 6). Clinical evidence-based guidelines recommend psychosocial interventions as first line of treatment (1, 2) with large body of scientific knowledge suggesting that these interventions can help improve CUD; especially, contingency management (CM) and cognitive-behavioral therapy (CBT) (1, 5–8).

Systematic reviews and meta-analysis testing the effectiveness of the available psychosocial interventions for individuals with CUD, converge in reporting the efficacy of CM programs either alone (7) or in combination with community reinforcement approaches (CRA) or with other CBT approaches [such as the relapse prevention treatment developed by Carroll et al. (9–11)] by increasing the abstinence period and reducing the dropout rates, which makes CM the most reliable method to turn an active cocaine user into an abstainer (5, 6). CM and CRA are two behavioral approaches, based on the principle of operant conditioning, where the substance related behavior is understood to be reinforced or maintained by its consequences. The previous (CM), provides an arbitrary reward in face of positive behavioral changes (i.e., most frequently drug-negative urine test), which typically consists of vouchers exchangeable for foods and services, and the latter (CRA) focuses on providing natural rewards by helping people adopt a more rewarding lifestyle free of drugs. However, in clinical practice, the above mentioned approaches are not often implemented (12) in part because they require some cost-effective changes such as the need for conducting higher urine tests or providing monetary rewards such as vouchers, thus the approach of Carroll et al. (13, 14) is a good evidence-based alternative.

With the new digital era, a new intervention window emerges through the implementation of web-based treatments that can intensify and optimize the current face-to-face treatment approaches. In fact, the current challenge in the treatment of CUD is in identifying innovative ways to implement the treatment rather than developing more effective strategies (5). However, literature in clinical settings is still scarce for addictive behaviors with very few studies on the effectiveness of web-based interventions for the treatment of illegal substance use. Up until now, much of this work has been conducted in the area of smoking, in which cognitive-behavioral interventions by means of computers/ internet have demonstrated to be effective on quit rates or attempts (15, 16). Thus, far, two web-based interventions have been tested through RCTs for treating CUD with positive effects reported in their target population (17, 18).

CBT4CBT is a CBT web-based treatment for substance use disorders. Previous studies conducted in US have shown its positive impact on improving face-to-face treatment as usual (TAU) (18–20). More specifically, participants who underwent CBT4CBT were significantly more likely to attain three or more weeks of continuous abstinence during treatment compared to participants who underwent TAU (18–20). These effects endured 6 months after treatment, measured through self-reported measures and urine toxicology screens (18, 20). Additionally homework adherence in CBT4CBT is associated with less cocaine use during treatment (19) and participants who completed at least 50% of homework displayed a greater cocaine use reduction in comparison with the ones who completed <50% of homework (21). Considering previous data regarding the prognosis and standard CUD treatment approaches, the evidence suggests that CBT4CBT approach concomitant to TAU could enhance current treatments and improve the outcomes in patients with severe CUD. In order to test the add-on efficacy of the web based CBT4CBT program concomitant to TAU, the comparative and the experimental group will have the same protocol of face-to-face sessions and will only diverge with the provision of the web based CBT4CBT program at the experimental group.

### Aims of the study

The aim of the present study is to evaluate whether adding a web-based cognitive behavioral therapy (CBT4CBT) to standard cocaine use disorder treatment improves treatment outcomes in a Spanish sample of patients with severe CUD (that require inpatient treatment). To do so, two primary outcomes are considered: (1) treatment retention (vs. dropout) and, (2) relapse (number of positive urine specimens submitted, percent negative urine screens, percent days of abstinence, self-reported frequency of cocaine use). As secondary outcomes the following variables are measured: craving, psychopathological symptoms, days of any drug use, CBT4CBT usability and treatment satisfaction.

The secondary objectives of the study are two-fold: (a) To explore differences between men and women in treatment response; (b) To explore if comorbid psychopathological symptoms, other addictive behaviors, craving and emotion regulation difficulties are predictive factors of treatment outcome at the end of inpatient treatment as well as at the end of the 8-week CBT4CBT + TAU or TAU and at follow-ups (1, 3, and 6 month).

## Methods

### Participants

Inpatients with a diagnosis of cocaine use disorder (DSM-5 criteria) referred for cocaine detoxification to our addictive behaviors' unit at the Hospital de la Santa Creu i Sant Pau in Barcelona (Catalonia, Spain) that are candidates for day care treatment after receiving inpatient detoxification will be asked to participate in the study.

All participants will be recruited prior to CUD treatment randomization. To enter the study participants will: (a) be aged between 18 and 65 years, (b) be hospitalized for cocaine detoxification as the main substance, (c) abstinent at the time of study assessment (from the third day of hospitalization), (d) be eligible to attend day care after hospitalization. Exclusion criteria will be: (a) indication of treatment for other substance use detoxification which is not cocaine, (b) presence of severe psychopathological or neuropsychological alterations that hinder the participation in the study, (c) opioid use disorder within 1 year prior to participation (this criteria includes maintenance treatment with methadone or another opioid substance), (d) lack of Spanish or Catalan knowledge or difficulties to read or write that hampers the participation in the study, (e) non-acceptance of the study procedures, such as the signing of informed consent.

### Sample size calculation

Accepting an alpha risk of 0.05 and a beta risk of 0.2 in a two-sided test, 37 subjects are necessary in each treatment arm to recognize as statistically significant a minimum difference of 2.1 points on treatment relapse (i.e.,: Number of positive urine specimens submitted; primary outcome) between the two groups. The common deviation is assumed to be 3.1. It has been anticipated a drop-out rate of 5%. The parameters implemented to estimate the sample size are based on previous studies with similar populations (19).

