## Data collection and assessment

### Assessment

There will be 6 time-point assessments: *TO-PRE:* within the inpatient unit, before starting psychological treatment but once the patients are stabilized from cocaine withdrawal; *T1-PRE:* after inpatient treatment before starting outpatient treatment (TAU or TAU + CBT4CBT); *T2-POST:* once the 8-w outpatient treatment is completed (TAU or TAU + CBT4CBT); *T3-FU: 1* month follow-up; *T4-FU:* 3 months follow-up; *T5-FU:* 6 months follow-up. Additionally, the presence of benzoylecgonine (metabolite of cocaine) in urine will be assessed weekly during the 8 w period of web-based treatment (see Table 2).

**Table 2 T2:** Schedule of enrolment, interventions and assessments.

**Indicator**	**Enrolment (inpatient treatment)**	**End of inpatient treatment**	**TAU + CBT4CBT/TAU (weekly control)**	**Post treatment (TAU + CBT4CBT/TAU)**	**Follow-up (1, 3, 6 m)**
Inclusion/exclusion criteria	XXXX				
Informed consent signature	XXXX				
Allocation	XXXX				
Sociodemographic data collection	XXXX				

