### Instruments

Primary outcome measures will be treatment dropout (two consecutive failures to attend and not answering the phone) and relapse (cocaine use: number of positive urine specimens submitted, percent negative urine screens, percent days of abstinence, self-reported frequency of cocaine use). Treatment dropout will be determined throughout the attendance at the appointments with the clinician (TAU or TAU + CBT4CBT), which will be carried out weekly during the 8-week period of treatment and at follow-up points. Relapse will be determined according to the participants' reports and throughout the presence of benzoylecgonine (metabolite of cocaine) in urine assessed with the Kinetic Microparticle Interaction test in a Solution (Roche Diagnostic System, Inc., Sommerville, NJ).

Secondary measures will cover sociodemographic variables and anthropometric measures (weight and high), cocaine craving, psychopathological symptoms and comorbidities, other addictive behaviors, personality traits, emotion regulation skills and CBT4CBT usability as well as treatment satisfaction.

Psychopathological symptoms and comorbid disorders will be assessed with a Clinical interview based on the DSM-5 diagnostic criteria for addictive behaviors, the MINI international neuropsychiatric interview (23), the Symptom CheckList-90 items-Revised (SCL-90-R) (24, 25), The State-Trait Anxiety Inventory (STAI) (26, 27) and the Beck's Depression Inventory (BDI) (28, 29). Craving and compulsive drug use will be measured with the following self-reported questionnaires: Severity of Dependence Scale (SDS) (30, 31), Cocaine Selective Severity Assessment (CSSA) (32, 33), Weiss Craving Scale (WCS) (34, 35). Other addictive behaviors will be measured, including gambling with the South Oaks Gambling Screen (SOGS) (36, 37), food with the Yale Food Addiction Scale 2 (YFAS) (38, 39), gaming with the DSM-5 criteria for internet gaming disorder (IGD) (40, 41) and sexuality with the Hypersexual Behavior Inventory (HBI) (42, 43).

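### The relapse measure that sizes the trial counts only positive urines submitted, so any retention benefit of CBT4CBT biases it against CBT4CBT, by an amount that depends on the retention gap

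*Protocol article*

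**What the plan says.** Under Sample size calculation, the protocol article powers the trial on "Number of positive urine specimens submitted; primary outcome". The target is "a minimum difference of 2.1 points on treatment relapse", and "The common deviation is assumed to be 3.1". The result is 37 patients per arm, with 5% dropout anticipated.

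Under Assessment, benzoylecgonine "in urine will be assessed weekly during the 8 w period of web-based treatment", so a patient can give at most 8 weekly specimens during treatment.

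Aims of the study names two primary outcomes, retention and relapse. Instruments defines relapse by several measures, beginning "number of positive urine specimens submitted, percent negative urine screens" and continuing with percentage of days abstinent and self-reported use. The same section defines dropout as two missed appointments in a row with no answer by phone. The article does not provide for urine collection after dropout, does not say how an unsubmitted specimen is scored, and does not state the denominator of the percentage of negative screens.

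The Introduction calls dropout in this disorder high. The Discussion mentions dropout after allocation, but only as a limit on power.

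**The concern.** In a count of positives submitted, a missed test and a negative test both score zero. Suppose a patient is positive on half of all weekly tests. That patient scores 4 if retained for 8 weeks, 2 if leaving after week 4, and 1 if leaving after week 2, with the same cocaine use while in treatment. Leaving therefore looks like improvement.

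This matters here because better retention is one of the effects that the trial is looking for. If CBT4CBT keeps more patients in treatment, its arm submits more specimens and can accumulate more positives. Success on the first primary outcome then pushes the powered measure of the second one the wrong way.

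**Working it through.** **The plan's own figure.** Inputs from Sample size calculation: difference 2.1, SD 3.1, two-sided alpha 0.05, power 80%, dropout 5%.

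n = 2 × 3.1² × (1.96 + 0.84)² / 2.1² = 34.2, rounded up to 35 per arm; 35 / 0.95 = 36.8, rounded up to 37. The stated size reproduces, so the arithmetic is sound. The question is about the measure.

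**Expected count under equal use.** Let p be the chance that a weekly specimen is positive, and R the share of patients still attending at week 8, with a constant weekly loss. The expected number of specimens submitted is S(R) = sum of R^(k/8) for k = 1 to 8, and the expected count is p × S(R). The article gives neither p nor R, so both are assumptions.

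Example, R = 0.70: the weekly factor is 0.70^(1/8) = 0.9564, and S = 0.9564 × 0.30 / 0.0436 = 6.58.

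With p = 0.5 in both arms:

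| Left by week 8, TAU / CBT4CBT | S, TAU | S, CBT4CBT | Spurious excess in CBT4CBT |
|---|---|---|---|
| 5% / 5% | 7.77 | 7.77 | 0 |
| 30% / 20% | 6.58 | 7.07 | 0.5 × 0.49 = 0.25 |
| 52% / 19% | 5.41 | 7.12 | 0.5 × 1.71 = 0.85 |

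The timing of loss matters a little. If everyone gives the week-1 specimen and loss then runs at 10% against 3% a week, 1 − 0.9^7 = 52% and 1 − 0.97^7 = 19% have left by week 8. The expected specimens are (1 − 0.9^8)/0.1 = 5.70 and (1 − 0.97^8)/0.03 = 7.21, and the excess is 0.5 × 1.51 = 0.76.

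Over p from 0.3 to 0.7 and retention pairs of 80/60, 80/40, 95/50 and 60/30 per cent, the excess runs from 0.30 to 1.57 specimens, which is 14% to 75% of the target 2.1.

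**How often a test would mislead.** Simulation with 37 per arm, 8 weekly tests, beta-binomial spread (SD = √(8 × 0.25 × (1 + 7/1.8)) = 3.13), no effect on use, and a t-test on the total submitted:
- 30% against 20% left: excess about 0.24; TAU wrongly favoured in about 6% of trials (5% to 6% across runs).
- 52% against 19% left: excess about 0.77; TAU wrongly favoured in about 20%.
- Nominal rate in that direction: 2.5%.

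**When there is a real benefit.** For illustration, take p = 0.60 under TAU and 0.3375 under CBT4CBT, a difference of 8 × 0.2625 = 2.1 if all 8 specimens were given.
- 5% left in both arms: 0.2625 × 7.77 = 2.04 remains.
- 50% against 20% left: 0.60 × 5.52 − 0.3375 × 7.07 = 0.93 remains.
- Smaller benefit, p = 0.5 against 0.4, with 60% against 20% left: 0.5 × 4.94 − 0.4 × 7.07 = −0.36, so the sign reverses.

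**Alternatives under equal use.** The proportion positive among submitted specimens has expectation p in both arms, so it shows no spurious difference when leaving is unrelated to use. Scoring missed tests as positive gives an expected 8 − S + pS. The arms then differ by (1 − p) times the gap in S, in favour of the better-retained arm. At p = 0.5 this mirrors the bias of the count: in the 52%/19% simulation it was about 0.74 in favour of CBT4CBT, significant in about 20% of trials.

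**The case against.** Several points on the other side are fair.

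- **Size.** The larger figures need a wide retention gap. The only dropout figure in the article is 5%, and at that rate in both arms the problem almost vanishes. This stands, although equal retention would mean no effect on the first primary outcome.
- **Stated analysis.** Data analysis names Cox regression and a mixed model of repeated measures, not a t-test on totals. Time to first positive does not accumulate positives, and a repeated-measures model need not score a missing week as zero. The artefact arises if the total itself is compared. The sample size calculation, with a difference and SD on the count, implies that comparison; Data analysis does not state it.
- **Other measures.** The percentage of negative screens is already listed under relapse. Taken over submitted specimens, it avoids most of the artefact. But the trial is not powered on it and its denominator is not given.
- **Unseen plan.** Missed-specimen rules often sit in an analysis plan. But under a count of specimens submitted, a missed test is not a missing value; it is simply not counted. That definition is fixed in this article.

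A reader might infer that the plan's 80% power collapses. The documents do not support that. The 2.1 is stated as a difference in specimens submitted and is said to come from previous studies, so it may already reflect non-submission. Treating it as a full 8-week difference and then subtracting dropout does not give the plan's own power. Nor do they support the view that a real benefit would generally be reversed: reversal needs a small benefit and a large retention gap together.

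**Conclusion.** The concern holds as a flaw in a stated measure. The count that sizes the trial is biased against whichever arm retains patients better, and retention is itself under test. Under equal use and the assumed loss rates, the bias is about 0.24 specimens at 30% against 20% left and about 0.77 at 52% against 19%, compared with a target of 2.1. It is absent when retention is equal. The direction follows from the definition. The size rests on assumed retention and positivity, and the error rates also assume a t-test on totals. The expected consequence is a diluted benefit rather than a false harm, although a wide retention gap with no effect on use could produce an apparent harm.

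**What to change.** Make the powered relapse measure the weekly benzoylecgonine result, positive or negative, over the 8 scheduled weeks. Compare all randomised patients with a repeated-measures logistic mixed model, an extension of the mixed model already named in Data analysis. Keep the raw count as descriptive, and state the denominator of the percentage of negative screens.

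Add sensitivity analyses for missed specimens. Scoring them as positive can be one, but the plan should say that it errs the opposite way, towards the better-retained arm, so it cannot stand alone.

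Recheck the 2.1 and 3.1 for the new measure. Dividing them by 8 does not show that 37 per arm carries over, because a logistic mixed model targets a different quantity.

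Cost: rewording, somewhat more analysis, and reliance on a missing-data assumption that is open to doubt if patients who relapse leave before giving a positive specimen. The change of measure needs no new data collection; the recheck will show whether 37 per arm is still enough.

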### Design and settings

This is an unicentric national open-label-randomized clinical trial focused on the improvement of cocaine use disorder treatment as usual (TAU) outcomes through the implementation of a web-based CBT treatment (CBT4CBT). The study was approved by the Research Ethics Committee of the Hospital de la Santa Creu i Sant Pau, project number IIBSP-CBT4CBT-2020-1116.

The present RCT has two arms: arm A (TAU) and arm B (TAU + CBT4CBT). All individuals with cocaine use disorder coming to our inpatient unit for cocaine detoxification will receive treatment as usual (TAU), which will consist of a multidisciplinary approach including psychiatrists, psychologists and nurses. The hospitalization for detoxification begins with the removal of all drugs and, during hospitalization, psychiatrists adjust medication in accordance to cocaine withdrawal symptoms. Additionally, individuals also receive daily psychological interventions based on motivation for change, craving management, assertive communication, problem solving skills and relapse prevention. Nursing staff carries out necessary therapeutic actions, such as taking vital signs, administering medications, provide space for emotional venting and conducting group therapies addressing motivation for change. After a mean of 14 days from admission, inpatients are discharged and placed to either TAU (day care treatment as usual + weekly outpatient follow up) or TAU + CBT4CBT (day care treatment as usual + weekly outpatient follow up and CBT4CBT). The intervention will be discontinued in case of request by the participant. Finally, to ensure adherence to intervention, after one unjustified absence rated by the psychologist, a phone call will be done (see Figure 1).

**Figure 1 F1:**
[figure not shown]
Study design.

Within the framework of the study and with the purpose of introducing the subsequent outpatient treatment, all patients in our inpatient unit for cocaine detoxification who are part of the study will also receive individual psychological CBT based treatment with motivational strategies, emotional regulation skills for mood symptoms and craving management, as explained previously. After completing the inpatient care (at discharge of inpatient care), patients will be randomly assigned to the CBT4CBT + TAU or to TAU. The randomization will be centralized through Clinapsis (http://www.clinapsis-estudis.com/) and all data will be handled through this same platform. Clinapsis is a friendly-user platform where all data from participants is stored. To ensure the transparency and the achievement of ethics procedures, the Central Clinical Research and Clinical Trials Unit of Research Institute of the Hospital de Sant Pau can access the platform to monitor the data collection and management. In addition, the two researchers who provide the psychological strategies during both the inpatient and outpatient treatment phase and carry out the assessments ([name] and [name]) also have access to Clinapsis to check whether all data is completed and, subsequently, export it to the software Statistical Package for Social Sciences (SPSS) v. 26.0. Once the database is crated in SPSS, authors will manage the database removing duplicates, identifying missing values and setting up all the variables in order to conduct the statistical analyses in SPSS. Any imbalance in the number of participants in each treatment arm due to non-adherence to treatment protocol prior to starting CBT4CBT but after arm allocation, will also be centralized through Clinapsis.

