### Web-based CBT intervention (CBT4CBT)

After completing the inpatient care (at discharge), the patients randomly assigned to the experimental condition will receive the TAU + CBT4CBT a web-based treatment which, as previously stated was tested on individuals with cocaine use disorder in America by the team of Carroll et al. (18). Depending on the patients' personal situation, they will have two options for receiving the treatment: they will be provided with access to the computer program in a small private room within the addictive behaviors outpatient unit or they will be provided with code access for being able to do it from home. In all instances, a psychologist will guide participants through their initial use of the CBT4CBT program and she will be available to answer questions and assist participants each time they use the program (the CBT4CBT and TAU treatments are always explained by a woman). The participants will access the program through an identification/password system to protect confidentiality.

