Researchers [name] and [name] monitor whether participants complete the modules of the CBT4CBT treatment and report it in a separate excel sheet. Also, the completion of the modules can be tracked entering to the section “providers” in the CBT4CBT website (http://www.cbt4cbt.com). Apart from whether the participant has completed or not the module, the researcher can check the percentage of completion of the module and the time spent on it.

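### Self-reported cocaine use, part of the primary relapse outcome, is collected by unblinded treating staff, so those measures are open to arm-related reporting bias of unknown direction and size

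*Protocol article*

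**What the plan says.** All references are to the protocol article.

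- **Blinding.** Design and settings: "This is an unicentric national open-label-randomized clinical trial".
- **Who treats and who assesses.** Design and settings, text after Figure 1: the "two researchers who provide the psychological strategies during both the inpatient and outpatient treatment phase and carry out the assessments". The same two "also have access to Clinapsis to check whether all data is completed and, subsequently, export it" to SPSS.
- **Knowledge of arm.** Web-based CBT intervention (CBT4CBT): researchers "monitor whether participants complete the modules of the CBT4CBT treatment and report it in a separate excel sheet". In the same section a psychologist introduces the program, and "she will be available to answer questions and assist participants each time they use the program".
- **Primary relapse measures.** Instruments lists four: "number of positive urine specimens submitted, percent negative urine screens, percent days of abstinence, self-reported frequency of cocaine use". On the data source it says: "Relapse will be determined according to the participants' reports and throughout the presence of benzoylecgonine". Aims of the study gives the same four measures.
- **Dropout, the other primary outcome.** Instruments defines it as two missed attendances in a row together with no answer by phone, judged from weekly clinician appointments and the follow-up visits. Separately, Design and settings describes an adherence step: "after one unjustified absence rated by the psychologist, a phone call will be done".
- **Sample size.** Sample size calculation uses the number of positive urine specimens, labelled there as the primary outcome: difference 2.1, SD 3.1, two-sided alpha 0.05, beta 0.2, 5% dropout, 37 per arm.

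The article describes no assessor who is independent of treatment or unaware of the arm. The limitations paragraph in the Discussion does not mention the matter.

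**The concern.** A patient's account of cocaine use is sensitive to who asks, and to what the patient believes that person hopes to hear. Here the staff carrying out the assessments also deliver the therapy and know the allocation, and the patient knows it too. If reporting differs between arms for reasons other than use, the difference passes straight into any measure built on the report. It can create or hide a treatment effect, and a larger sample does not remove it.

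This matters because self-report is not a supporting measure in this plan. It has the same primary status as the urine measures. A result on self-reported frequency or days abstinent could be presented as a primary finding even though it carries a bias that the urine results do not directly share.

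**Working it through.** **1. Reproduce the plan's own figure.** Inputs from Sample size calculation: difference 2.1, SD 3.1, alpha 0.05 two-sided, power 0.80.

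n per arm = 2 × [SD × (1.960 + 0.842) / difference]² = 2 × [3.1 × 2.802 / 2.1]² ≈ 34.2, rounded up to 35.

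With 5% dropout: 35 / 0.95 = 36.8, rounded up to 37. The stated 37 per arm reproduces. It rests on a urine count, so the present point does not disturb it.

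**2. Sort the primary measures by exposure to reporting.**

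| Measure | Source | Directly exposed to reporting? |
|---|---|---|
| Number of positive urine specimens | Laboratory assay | No; the number submitted depends on attendance |
| Percent negative urine screens | Laboratory assay | No; same remark |
| Percent days of abstinence | Not stated. Urine is weekly during the 8 weeks (Assessment), which cannot show daily abstinence, so self-report is the reasonable reading | Yes, on that reading |
| Self-reported frequency of use | Participant report | Yes |

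Dropout is based on attendance and phone contact, not on reported use.

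**3. Illustrate the consequence.** The documents give no size for any reporting bias, so a range is assumed. Let b be an arm-related shift in a self-reported measure, in SD units, with no true effect and m patients per arm. The test statistic is then centred at b / √(2/m) instead of 0, and

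error rate = 1 − Φ(1.96 − b/√(2/m)) + Φ(−1.96 − b/√(2/m)).

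For m = 37, 1/√(2/37) = 4.30. At b = 0.2 the centre is 0.86.

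| Assumed shift b (SD) | 37 per arm | 35 per arm |
|---|---|---|
| 0 | 5% | 5% |
| 0.1 | 7% | 7% |
| 0.2 | 14% | 13% |
| 0.3 | 25% | 24% |
| 0.5 | 58% | 55% |

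The centre grows with √m, so at a fixed shift more patients make a false positive more likely. The table shows sensitivity to an assumed shift. It does not show that such a shift will occur.

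**The case against.** The strongest defence is that the arms are treated alike. The Introduction gives both groups the same face-to-face protocol, differing only in the web program, and the two researchers are not described as split by arm. Under-reporting to one's own therapist would then be common to both arms and would largely cancel in the comparison. The article also does not say how use reports are collected, so they may already be self-completed. The sample size rests on an objective assay.

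Much of this stands. It limits what can be claimed, and several stronger readings that a reader might infer are not supported:

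- **That under-reporting will be greater in the CBT4CBT arm.** The text says only that a psychologist is available during program use, and it allows use from home. It does not say that she is one of the two assessing researchers, though that is likely. The direction is conjecture.
- **That the psychologist's rating of absences directly biases dropout.** The dropout definition in Instruments does not require an absence to be unjustified. The rating prompts a phone call meant to support adherence, and that call is not said to be the one in the definition. Any link is indirect.
- **That a positive urine would leave a report of abstinence uncorrected.** The article does not say this. A rule for disagreement may properly sit in the analysis plan, so its absence here is no fault.
- **That the two researchers could assess each other's patients as a remedy.** Both know the arm, so this would blind no one.

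What the defence does not answer is the stated allocation of roles. Identical procedures do not guarantee identical reporting when patient and assessor both know the arm, and the self-reported measures have equal primary standing with urine.

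**Conclusion.** The point holds in a limited form. As written, self-reported cocaine use within the primary relapse outcome is collected by treating staff who know the arm. That exposes self-reported frequency and, on the reasonable reading above, percent days of abstinence to bias that could differ by arm: two of the four relapse measures. The urine assay results are not directly affected, and the sample size stands.

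Direction and size are unknown. The 7% to 58% range is illustrative; it assumes 37 per arm, no true effect, a normal approximation and a shift of 0.1 to 0.5 SD. Patients cannot be blinded to a web program, so the remediable part is the status given to self-report and the way it is collected. This is a worthwhile and inexpensive improvement, not a defect that undermines the trial.

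**What to change.** 1. Name the number of positive urine specimens, the measure the sample size already uses, as the confirmatory relapse measure. Treat the self-reported measures as supportive.
2. Have patients complete the substance-use report themselves, before the session and before the urine result is known. If this is already the practice, say so.
3. Where report and urine are combined, let a positive benzoylecgonine test override a report of no use in the period the test covers, identically in both arms. Report by arm how often urine is positive and the report negative.
4. For the dropout outcome, count failures to attend from the appointment log, identically in both arms. The adherence phone-call procedure stays as it is.

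**Cost.** The self-reported measures lose confirmatory status. There is minor scheduling work for self-completion and a small amount of extra analysis for discordance. No additional staff, procedure or patients are needed, and 37 per arm is unchanged.
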